### Randomisation

Children will be assigned using stratified random sampling. Before intervention (T1), children will be first stratified according to the House Functional Classification Scale (4–5 vs. 6–7), age (6-9y vs. 10–12 y), and the type of CST wiring pattern (contralateral, bilateral and ipsilateral) assessed by Transcranial Magnetic Stimulation (TMS) to maximize homogeneity and minimize group differences at baseline. A permuted block design of two will then be used, created by a computer random number generator to randomize the participants to the mCIMT+AOT or mCIMT alone group within each stratum. Randomization will be performed by an independent person who is not involved in the selection procedure and cannot access the clinical information of the children.

### Sample size

Sample size estimate is based on the primary endpoint, which is defined as the immediate effect of the intervention on the primary outcome measure, i.e. bimanual performance measured with the Assisting Hand Assessment (AHA). The smallest detectable difference has been reported to be 5 AHA units [24]. A previous intervention study of intensive therapy in children with uCP [6], reported a standard deviation of 5.5 AHA units, which would translate into an effect size of 0.9. With this effect size, an alpha-level of 0.05, and a statistical power of 0.80, a sample size of 21 children is needed in each group to detect a difference equal to or larger than the smallest detectable difference of 5 AHA units between groups [24, 25]. Sample size estimates were calculated with G*Power [26, 27].

### Blinding

In order to blind parents and children to group allocation, they will only be informed about the general description of the study design. However, they will not be informed about the type of observation the children eventually receive (AOT or control condition). All therapists and study personnel assisting during the intervention will not be blinded of group allocation. One blinded, experienced physiotherapist, not involved in the camp activities, will assess UL function at the four different time points. Video-based clinical scales (AHA and Melbourne Assessment 2) will be scored afterwards by another evaluator, blinded to group allocation and time point of the assessment. The 3DMA will be performed by two experienced physiotherapists not blinded to group allocation, as these analyses are fully automated.

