This study protocol describes the set-up for a single blind randomized controlled trial (RCT) comparing the effects of mCIMT with or without AOT on UL function using both clinical and kinematic outcomes. The first objective is to examine whether combining mCIMT with AOT will augment the treatment effects and result in longer retention. Secondly, the potential role of the anatomical characterization of the brain lesion, structural and functional connectivity and the CST wiring in predicting treatment response will be investigated. These findings might aid in guiding patient selection for tailor-made intervention programs in children with uCP.

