##### Three-dimensional motion analysis

Upper Limb Three-Dimensional Motion Analysis (UL-3DMA) will be conducted at T1, T2 and T3. A custom-made chair with foot and back-support is used to perform the measurements in a standardized sitting position. A total of 17 reflective markers (14 mm diameter) are attached to the trunk, acromion, upper arm, forearm, and hand. Next, several static calibration trials are conducted to identify anatomical landmarks of interest, following the guidelines of the International Society of Biomechanics [52]. The movement protocol contains eight tasks: three reaching tasks (forwards, RF; upwards, RU; sideways, RS), two reach-to-grasp tasks (grasp a sphere, RGS; grasp a vertical cylinder, RGV) and three daily-life activities mimicking tasks (hand-to-head, HTH; hand-to-mouth, HTM; hand-to-shoulder, HTS). Each task was performed four times within two trials, resulting in eight movement repetitions per task. Tasks were executed with the impaired UL at self-selected speed. Each task is started in upright sitting with 90° of hip and knee flexion, with the impaired hand on the ipsilateral knee. This protocol has been proven reliable in children with uCP [53]. To record motion, 12 to 15 Vicon infrared cameras (Oxford Metrics, Oxford, UK) sampling at 100 Hz will be used to capture the UL movement patterns. Offline data processing will be performed with Vicon Nexus software (version 1.8.5, Oxford Metrics, Oxford, UK) and consists of a Woltring filtering routine with a predicted mean squared error of 10 mm^2^ [54], gap filling, and selection of the movement cycles (start (hand on ipsilateral knee) and end of each movement cycle). Task end-point is defined as follows: (1) touching the spherical object with the palm of the hand (RF, RU and RS), (2) grasping (sphere (RGS) or vertical cylinder (RGV)), and (3) touching different parts of the body (top of the head (HTH), mouth (HTM) or contralateral shoulder (HTS)). To avoid start and stop strategies of the child, only the middle two repetitions of each trial will be analysed, resulting in four analysed movement repetitions per task. Lastly, we time-normalize the movement cycles (0–100%) and calculate the root mean squared error (RMSE) of the kinematic angles of each cycle to compare it to the mean of the remaining 3 cycles (per task). As such, we retain the 3 cycles with the lowest RMSE for further analysis, which represent the most reliable movement patterns. The open source software ULEMA v1.1.9 [53, 55, 56] will be used to calculate the kinematics of five joints with a total of 13 angles: trunk (rotation, lateral flexion and flexion-extension), scapula (tilting, pro-retraction and rotation), shoulder (rotation, elevation plane and elevation), elbow (flexion-extension and pro-supination) and wrist (flexion-extension and ulnar-radial deviation). Spatiotemporal parameters, joint kinematics and summary indices will be calculated and used for statistical analysis.

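### Automation of the later processing steps does not justify leaving the whole three-dimensional motion analysis unblinded

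*Protocol article*

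**What the plan says.** Under Blinding, one blinded physiotherapist assesses upper limb function at all four time points. The AHA and Melbourne Assessment 2 videos are then scored by another evaluator who knows neither the group nor the time point. The motion analysis is treated differently: "The 3DMA will be performed by two experienced physiotherapists not blinded to group allocation, as these analyses are fully automated".

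The section Three-dimensional motion analysis sets out what this assessment involves. On capture it says "A total of 17 reflective markers (14 mm diameter) are attached to the trunk, acromion, upper arm, forearm, and hand", and then "several static calibration trials are conducted to identify anatomical landmarks of interest". The child performs eight tasks at a self-selected speed. Offline processing in Vicon Nexus consists of a Woltring filter with a fixed parameter, then "gap filling, and selection of the movement cycles". A cycle starts with the hand on the knee of the same side. It ends with the palm contacting the sphere, with a grasp, or with the hand reaching the head, mouth or opposite shoulder. After that, "only the middle two repetitions of each trial will be analysed, resulting in four analysed movement repetitions per task". The cycles are time-normalised, the three with the lowest RMSE are kept, and ULEMA computes 13 angles. Spatiotemporal parameters, joint kinematics and summary indices all enter the statistical analysis.

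The Background describes a trial comparing the two treatments "on UL function using both clinical and kinematic outcomes". The motion analysis is placed under Secondary outcome measures.

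**The concern.** The protocol gives a reason for an exception to blinding, and its own account of the method does not bear that reason out. Automation protects against assessor bias only in the steps that are automated. If the person who places markers, runs the session, fills gaps or fixes the start and end of a cycle knows the child's group, expectation can enter before any computation begins.

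Cycle limits matter most. They determine movement duration directly, and they rescale every curve expressed on 0–100% of the cycle. At stake is the credibility of any between-group difference in the kinematic outcomes. The protocol already applies the natural safeguard, masking to group and time point, to the AHA and Melbourne Assessment 2 videos. It describes none for the motion files.

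**Working it through.** No figure in the plan belongs to this point. The sample size rests on the AHA and has no bearing here. The check compares the stated reason with each described step.

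**Step by step**

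| Step | Stage | Does the document give an automatic rule? |
|---|---|---|
| Attaching 17 markers | Capture | No; hands-on by nature |
| Static calibration for landmarks | Capture | No; depends on the operator |
| Running a task at self-selected speed | Capture | No |
| Woltring filter | Processing | Yes, fixed parameter |
| Gap filling | Processing | Not stated |
| Selecting cycle start and end | Processing | Events defined, but no threshold or detection algorithm |
| Middle two repetitions | Processing | Yes |
| Time normalisation | Processing | Yes |
| Three lowest-RMSE cycles | Processing | Yes |
| ULEMA angles | Processing | Yes, computed |

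Five of the ten steps are covered by a stated rule or computation. Five are not: three in capture and two in processing.

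**Do the later rules remove the problem?** Let a cycle run from t_start to t_end, so that duration = t_end − t_start. Suppose an operator places every end event later by δ.
- Each duration becomes (t_end + δ) − t_start, which is the former duration plus δ. If the same three cycles are kept, their mean also rises by δ.
- The RMSE rule compares each cycle with the mean of the other three. A shift common to all four leaves them about as alike as before, so the rule does not screen it out. It removes the odd cycle, not a consistent displacement.
- If the average δ differs between groups, that difference passes one-for-one into the group difference in duration. Sampling is at 100 Hz, so one frame is 1/100 = 0.01 s. Each frame of average difference in placement adds 0.01 s. This is a conversion only; the document gives no basis for saying how many frames, if any, would be involved.

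**How much of the data passes through these steps?** Two trials with two repetitions each give 2 × 2 = 4 analysed repetitions per task. Eight tasks give 8 × 4 = 32 cycles per child and session. T2 and T3 together give 2 × 32 = 64 cycles, each with a selected start and end. All kinematic data at these visits are therefore downstream of cycle selection.

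**Which time points?** Stratification and randomisation take place around T1, so T1 capture may precede knowledge of allocation. T2 and T3 capture follow it. The document does not say when T1 files are processed offline; if that is after allocation, their processing is exposed too.

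**The case against.** The strongest reply is that the document never calls gap filling or cycle selection manual. Both are listed as processing in Vicon Nexus and might be scripted, and a condensed article may leave event detection to the full protocol. This stands in part. A reader might infer that the protocol admits to manual, judgement-based processing; it does not. That these two steps involve operator choice is a reading, supported by the contact and grasp end-points and by the absence of any stated detection rule.

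A second reply is that the reason speaks of analyses, whereas marker placement and calibration are acquisition, so there is no strict contradiction. That is fair. But on that reading the reason does not reach the capture session at all, although the rule leaves those who perform the whole assessment unblinded. Either way the justification falls short of what it is used for.

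A third reply is that discretion is limited: the start position is fixed, end-points are defined by task, the repetitions to analyse are prescribed, and the movement protocol is described as reliable in this population. This stands as a limit on the room for bias. Reliability, however, concerns random disagreement and does not exclude a shift that follows group.

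Two further inferences are tempting. One is that kinematics form part of the first objective. The sentence naming clinical and kinematic outcomes describes the trial set-up; the objective that follows it names no outcome type. The other is that the evaluator-blinded label is undermined as a whole. It is not, because the AHA is scored by a blinded evaluator and the Blinding section openly says that the motion analysis is unblinded.

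**Conclusion.** The point holds in a limited form. Full automation, the only reason offered, does not justify unblinded motion analysis as a whole, because the protocol describes operator-dependent capture and two processing steps without a stated automatic rule. The secondary kinematic outcomes, mainly at T2 and T3, are open to assessor bias. Its size and direction cannot be derived from the document, and none is claimed. The primary AHA outcome is unaffected.

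The conclusion on capture needs no assumption beyond what marker placement and calibration involve. The conclusion on processing rests on two assumptions: that gap filling or cycle selection leaves some choice to the operator, and that the unblinded physiotherapists, or others who know the group, do this work. If the full protocol specifies automatic event detection and gap filling, only the capture part remains. This is an improvement worth making to a secondary outcome, not a threat to the main result.

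**What to change.** Before offline processing, have an existing team member who will not process the files replace the child, group and time-point labels on the Vicon files with random codes and hold the key. Include the T1 files, so that time point is masked as well. Lock gap filling and cycle selection before the codes are opened.

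In the Blinding section, replace the statement about full automation with an accurate account: which steps are computed or rule-based, which depend on an operator, and how the latter are masked. If event detection is in fact algorithmic, state the rule. File coding does not blind capture, so report motion capture as unblinded. A reader might suggest using whichever physiotherapist did not work in a given camp. The document does not say that these staff work in the camps, and absence from a camp would not by itself conceal allocation, so this cannot be relied on.

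The cost is one procedure paragraph, minor administration and a short delay before processing. No new visit, equipment or assessor is needed, only some time from an existing team member for the coding.

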### Treatment protocol

A day camp model will be used during which children receive intensive therapy for 6 hours a day, for 9 out of 11 consecutive days, with no therapy during the weekend (total of 54 h of therapy). Child/therapist ratio will be 1:1 to secure individual guidance. Experienced paediatric physiotherapists will lead the camps, assisted by physiotherapy master students, specialized in paediatric rehabilitation.

During the camps, all children wear a tailor-made hand splint on the less impaired UL while performing unimanual exercises based on (1) shaping and repetitive practice during individual therapy (9 h), (2) group activities (30 h) and (3) action-observation training or control condition (15 h). The theme throughout the camp is ‘Zora’, a rehabilitation robot that will welcome and motivate the children to engage in the activities. The splint is a rigid orthosis, individually adjusted and covering fingers, thumb, and wrist.

#### Individual therapy

One hour per day the child receives individual therapy based on motor learning principles of shaping and repetitive practice. Four goals will be trained that focus on the most commonly reported UL problems: active wrist and elbow extension, forearm supination, grip strength and fine motor tasks. The main investigators developed a manual encompassing exercises for these four goals embedded in functional activities. Individual guidelines for each child will be set up, based on baseline body function measures and video-based assessments of the Melbourne Assessment 2 (see evaluation for more details). Each child will exercise the four goals within a rotation system, in which each goal is practiced for 15 min taking the individual guidelines of the child into account. The degree of difficulty of the exercises and therapy equipment will be adapted daily to the child’s progress.

#### Group activities

The group activities will consist of varied activities such as painting, cooking, crafts and outdoor games. These activities will be selected and adapted to stimulate intensive use of the more impaired hand. This was further ensured by the one-on-one guidance. The activities will be uniquely performed with the more impaired hand. In activities demanding the use of two hands, the children will cooperate in pairs with each other or with the therapist.

#### Action-observation training

Children in the experimental group will receive a total of 15 AOT sessions of one hour, which is 1 or 2 h per camp day. The AOT program will be in line with the one described by Sgandurra et al. [13, 28]. However, the bimanual tasks will be replaced by unimanual activities, in order to keep the focus on unimanual training. During AOT, the children will watch video sequences showing unimanual goal directed actions. Two series of activity sets are developed, adapted according to the UL functional level of the child: one for children with House Functional Classification 4 or 5 (see Additional file 1: Table S1) and one for those with House Functional Classification 6 to 8 (see Additional file 2: Table S2). The set-up and the goal of the activities is similar, although the type of movement is simplified for the children classified in level 4–5. Both in the videos as well as during the execution of the tasks, all the material is placed on dark surface to highlight the contrast and facilitate the focus on the activity, in particular for those with a visual and/or attention problem. To avoid potential mental rotation, all videos will be shown in the perspective of the child (i.e. first-person perspective and side of the impaired hand is performing the action, where only the arm and hand are visible). The children will sit 50 cm in front of a computer screen of 22 in.. A therapist will sit next to the child on the more impaired side. In total, the AOT will consist of 15 tasks, one for each session, and each task will consist of three sub-activities. One action will be repeated for a total duration of 3 minutes. After watching this video sequence, the child will execute the observed actions with the more impaired UL repeatedly for 3 minutes. Each video will be performed twice. As such, a total of six video sequences are shown during one therapy session. While watching the videos, the therapist will keep the attention of the child focused on the shown actions. During the execution of the action, the therapist will verbally stimulate the child without giving any suggestive remarks (regarding movement quality) or providing a demonstration.

The children in the control group will watch video games not showing any human movements and not requiring any manual actions of the child because the therapist seated next to the child will control the keyboard and mouse. Afterwards, these children will practice the same tailored actions for 3 minutes in the same order as the experimental group. Verbal instructions will be given by the therapist without suggestive remarks or a demonstration of the task performance.

### Clinical evaluation

The clinical evaluation takes place in the Clinical Motion Analysis Laboratory of the University Hospitals Leuven.

#### Descriptive and clinical characteristics

General patient’s characteristics, such as age, more impaired side, and co-morbidities, will be recorded at baseline. Children will be classified according to the House Functional Classification System (HFC) and the Manual Ability Classification System (MACS). The HFC is a nine-level functional classification system, describing the role of the assessed hand as a passive or active assist in bimanual activities from 0 ‘does not use’ to 8 ‘uses hand completely independently without reference to the other hand’. This scale has been found to be reliable to classify unimanual function in children with spastic CP [29, 30]. The MACS reliably classifies the ability to handle objects in daily activities in children with CP between 4 and 18 years [31, 32]. It ranks the children on a five-level scale (level I = ‘Handles objects easily and successfully’; level V = ‘Does not handle objects and has severely limited ability to perform even simple actions’).

#### Cerebral visual impairment questionnaire

The Cerebral Visual Impairment (CVI) questionnaire was developed to screen children who may suffer from this impairment. This questionnaire is filled in by the parents and consists of 46 closed ended items clustered in six domains, evaluating visual attitude, ventral and dorsal stream functions, complex visuomotor abilities, use of other senses, and associated CVI characteristics. The CVI questionnaire has shown good sensitivity and specificity [33]. This questionnaire will serve as a starting point to determine whether the child may present with CVI and, therefore, may have some difficulties in observing the videos of the action-observation training.

#### Sensory function

Sensory assessments will be measured before the intervention (T1). They will comprise exteroception (tactile sense), proprioception (movement sense), two-point discrimination (Aesthesiometer®) and stereognosis (tactile object identification). These sensory assessments will be carried out following the protocol defined by Klingels et al. [34], which has been shown to be reliable in this population. Furthermore, a kit of 20 nylon monofilaments (0.04 g - 300 g) (Jamar® Monofilaments, Sammons Preston, Rolyan, Bolingbrook, IL, USA) will be used to determine threshold values for touch sensation [35]. This assessment has also shown to be reliable in children with uCP [36].

#### Mirror movements

Mirror movements will be evaluated before the intervention (T1). First, the occurrence of mirror movements will be scored during three unimanual tasks: (1) fist opening and clenching, (2) thumb-finger opposition, and (3) alternate finger tapping on a table surface. Each task will be performed five times with both hands separately, starting with the more impaired hand. Task execution will be video recorded and mirror movements will be scored following the 4-point ordinal scale of Woods and Teuber [37]. Second, the Grip Force Tracking Device (GriFT Device) will be used to evaluate mirror movements during repetitive unimanual squeezing while playing a computer game [38]. This portable device consists of two identical handles containing force sensors. First, the maximum voluntary contraction of each hand is calculated. Next, the children are asked to repetitively squeeze with one hand while playing a computer game. The rhythm is determined by a visual cue with a frequency of 0.67 Hz at 15% of the previously determined maximum voluntary contraction. Mirror movement characteristics such as frequency, strength and temporal features (synchronization and time lag) will be extracted, following the protocol described by Jaspers et al. [38].

### Outcome measures

UL function will be comprehensively evaluated on the levels of body function and structure, activity and participation following the ICF model.

